## Abstract

**Background**: Attention Deficit Hyperactivity Disorder (ADHD) is associated with executive function deficits—such as planning, organization, and prospective memory—that impair autonomy and daily functioning, increase family stress, and create challenges in educational contexts. These consequences underscore the need for accessible and ecologically valid interventions addressing the cognitive, familial, and educational dimensions. Traditional approaches often lack ecological validity, and pharmacological treatment shows a limited impact on functional cognition. **Objectives**: This protocol outlines a feasibility study of DiverAcción, a web-based telerehabilitation system designed to enhance functional cognition through interactive and gamified tasks integrated into a comprehensive healthcare programme. **Methods**: A quasi-experimental feasibility study before and after the study will recruit 30 participants aged 9 to 17 years with ADHD. The study comprises an initial face-to-face session for instructions and baseline assessment (T0), followed by twelve supervised online sessions over six weeks. Therapeutic support is provided via integrated chat, email, and two scheduled videoconference check-ins. **Feasibility Outcomes**: include recruitment, adherence, retention, usability (SUS), acceptability (TAM), satisfaction, user-friendly design, therapeutic alliance (WAI-I), and professionals’ attitudes toward technology (e-TAP-T). **Exploratory Measures**: include parental self-efficacy (BPSES), parenting stress (PSI-4-SF), ADHD symptomatology (SNAP-IV), executive functioning (BRIEF-2), time management (Time-S), emotional regulation (ERQ-CA), prospective memory (PRMQ-C), and health-related quality of life (KIDSCREEN-52). Analyses emphasize descriptive statistics for feasibility metrics (recruitment, adherence, retention, dropout and fidelity). Assessments are conducted post-intervention (T1) and at three-month follow-up (T2) and analyzed relative to baseline using repeated-measures ANOVA or Friedman tests, depending on data distribution. **Conclusions:** This feasibility protocol will provide preliminary evidence on the usability, acceptability, and implementation of DiverAcción. Findings will guide refinements and inform the design of a subsequent randomized controlled trial.

## 1. Background

Attention-Deficit/Hyperactivity Disorder (ADHD) is one of the most common neurodevelopmental conditions in childhood and adolescence (≈5–7%), and is associated with executive function (EF) deficits—particularly planning, organization, and prospective memory (PM)—that compromise autonomy in daily living, school participation, and family well-being. These characteristics highlight the need for interventions with strong ecological validity that address not only cognitive processes but also the family and educational contexts where change must occur. Pharmacological treatment remains first-line, yet its impact on functional cognition is limited; likewise, many psychological approaches show modest transfer to real-world performance [1,2].

Across development, EF follows a non-linear trajectory with rapid gains from early to mid-adolescence, decelerating improvement toward late adolescence and relative stabilization into adulthood; complex planning may continue to improve into the early twenties. PM also shows distinct profiles for event-based versus time-based demands, with the latter placing heavier self-monitoring loads. In ADHD, EF and PM often present uneven and protracted trajectories alongside common difficulties in emotion regulation (ER), which can exacerbate task initiation and execution. These findings have direct implications for intervention design: scaffolding metacognition (plan–monitor–evaluate), grading autonomy by age band, and explicitly supporting time-based PM and ER are key to feasibility and transfer [3,4,5,6,7,8,9,10,11].

Traditional cognitive rehabilitation has prioritized isolated process training (e.g., attention, memory) using repetitive, decontextualized tasks. Evidence suggests that improvements achieved in clinic rarely generalize to meaningful participation. In contrast, functional cognition refers to how cognitive abilities underlying occupational performance are integrated and applied to plan, organize, monitor, and complete meaningful tasks in real-world contexts, thus supporting autonomy and occupational participation. This paradigm emphasizes strategy use within everyday activities, environmental adaptations, and personally relevant goals to enhance transfer and sustained change [12,13,14,15].

Occupational therapy programs for ADHD adopt ecological approaches combining explicit EF training with caregiver mediation. Cog-Fun demonstrates short-term improvements by training planning, organization, inhibition, monitoring, and ER through meaningful, family-involved activities (≈10 sessions in childhood; 17–20 in adolescence). POET provides eight sessions of parent-focused coaching (home routines, parental EF), improving routine management and perceived competence; POET-T adapts the model to teachers and classroom cycles (6–8 weeks), enhancing participation though with limited global EF change. These models share ecological validity but differ in agents, dosage, and delivery context, and there remains a gap regarding multimodal integration and explicit training of time-based PM to support cross-context generalization [16,17,18,19,20,21,22].

Emerging digital tools—including virtual reality and web-based telerehabilitation—enable controlled yet realistic task demands, facilitate motivation and accessibility, and can reduce logistical barriers while supporting strategy transfer to natural contexts. DiverAcción was conceived to address the above gaps through an integrated, ecologically valid, web-based program that (1) explicitly trains EF (planning, organization, time management) and PM (with emphasis on time-based demands), (2) embeds ER supports, and (3) actively involves parents and teachers to promote generalization across home–school settings. The program combines a collaborative agenda (daily plan–monitor–evaluate scaffold), gamified training sessions, and structured caregiver sessions/supervision, aligning developmental needs with age-banded adaptations [23,24].

Finally, consistent with international guidance for developing child–adolescent digital mental health interventions and with the SPIRIT/CONSORT-eHealth framework, a feasibility evaluation is a necessary first step prior to an efficacy randomized controlled trial, focusing on usability, acceptability, adherence, and preliminary change signals in functional cognition domains relevant to everyday life [25,26,27,28].

## 2. Methods

### 2.1. Design

This feasibility study of DiverAcción adopts a quasi-experimental pretest-posttest design without a control group, following the Medical Research Council (MRC) guidelines for complex interventions [29,30] and the SPIRIT 2025 guidelines [26]. This protocol was developed and reported in accordance with the CONSORT extension for pilot and feasibility trials, the SPIRIT 2025 guidelines for trial protocols, and the CONSORT-eHealth checklist for digital interventions [26,27,28]. This is a feasibility trial; a full protocol registration will be completed after analyzing feasibility outcomes and incorporating any necessary adaptations. The trial registry identifier will be provided once the definitive protocol is submitted. The Supplementary Material provides an integrated checklist for each guideline.

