#### 2.9.2. Feasibility Outcomes

The primary aim of this study is to assess feasibility across multiple domains, following established frameworks for pilot and feasibility trials [52,67,68]. Progression criteria for feasibility outcomes are summarized in Table 3 and Figure 2.

The following outcomes will be evaluated:

*Recruitment and Retention*

Recruitment will be measured as the proportion of eligible participants who consent to participate, and the average recruitment rate per month. Retention will be defined as the percentage of participants who complete all planned assessments at T1 (post-intervention) and T2 (follow-up).

*Data Completeness and Missing Data*

Data completeness will be calculated as the proportion of participants providing valid data for each measure at each time point. Patterns and reasons for missing data will be documented. This information will inform the feasibility of data collection procedures and guide refinements for a future trial. Primary feasibility analyses will use complete cases. Sensitivity analyses using multiple imputation may be performed for exploratory clinical outcomes, but the results will be interpreted with caution given the small sample size.

*Adherence*

Adherence will be assessed based on three components:(a)use of the digital agenda on at least 80% of intervention days (over 6 weeks),(b)completion of at least 80% of scheduled online training activities, and(c)attendance at 100% of planned videoconference sessions.

Adherence will be reported as the proportion of participants meeting these criteria.

*Intervention Fidelity*

Fidelity will be ensured through a structured process: all occupational therapists delivering the intervention will complete a 20-h training course prior to implementation, covering theoretical foundations, intervention procedures, and use of digital tools. Fidelity will be monitored using session checklists, regular supervision meetings, and ongoing remote support. Fidelity will be categorized as high (≥80% of protocol elements delivered), moderate (60–79%), or low (<60%).

*Acceptability and Usability*

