### 2.12. Ethics and Dissemination

The DiverAcción study will be conducted in accordance with the ethical principles of the Declaration of Helsinki and applicable national and international regulations for research involving human subjects. Respect for the autonomy, privacy, and protection of participating minors and their families will be always guaranteed.

The protocol has been approved by the Local Biomedical Research Ethics Committee and complies with the requirements of Royal Decree 192/2023, of 21 March, which regulates medical devices, and Royal Decree 1090/2015, of 4 December, concerning clinical trials with medicinal products.

Since the participants are minors, their inclusion in the study will require the written informed consent of their legal guardians and the minor’s assent, after they have received clear information adapted to their level of understanding about the objectives, procedures, potential risks, and benefits of the study. Participation will be voluntary and may be discontinued at any time without negative consequences.

The DiverAcción telerehabilitation web platform will be provided free of charge by the local University, which will maintain the technical records and version control of the system used for research purposes. A member of the research team will be responsible for the supervision and proper use of the system during the study.

The personal and clinical data of the participants will be processed in a pseudonymous manner and in accordance with current legislation, as detailed in the data management plan included in the Data Management section.

The results of the study will be disseminated through publications in peer-reviewed scientific journals, national and international conferences, and institutional channels of the University of Granada. In addition, informative summaries will be prepared for participating families and associations, with the aim of facilitating the understanding and application of the findings in clinical and educational contexts.

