User-friendly design	Visual analog scale from 1 to 10	T1	Children and Adolescents Parents Teacher Occupational Therapists
Participant satisfaction	Participant Satisfaction Questionnaire	T1	Children and Adolescents Parents Teacher Occupational Therapists
Therapeutic Alliance	WAI-I	T1	Children and Adolescents
Executive functioning	BRIEF-2 for parents and teachers TEXI Inventory	T0, T1, T2	Parents and Teachers Children and Adolescents
Time management of children and adolescents	Time-S questionnaire EMT	T0, T1, T2	Children and Adolescents Teachers
Prospective Memory	PRMQ-C Automated metrics recorded by the platform	T0, T1, T2 T1	Children and Adolescents
Emotion regulation strategies in everyday life	ERQ-CA	T0, T1, T2	Children and Adolescents
Health-related quality of life (HRQoL)	KIDSCREEN-52	T0, T1, T2	Children and Adolescents
Parents’ perceptions of their parenting competence	BPSES	T0, T1, T2	Parents
Parental stress levels	PSI-4-SF	T0, T1, T2	Parents

Note: T0 = baseline, T1 = immediately post-intervention, T2 = 3 months after intervention.

**Table 3 healthcare-14-00323-t003:** Progression Criteria for Feasibility Outcomes.

Domain	GO (Proceed)	AMEND (Modify)	STOP (Do Not Proceed)
Recruitment	≥70% of eligible approached	50–59%	<50%
Retention	≥80% at T1/T2	60–79%	<60%
Data completeness	≥80% completeness	70–79%	<70%
Adherence	≥80% agenda & training; 100% videoconferences	60–79% agenda/training	<60% agenda/training
Fidelity	≥80% protocol elements delivered	60–79%	<60%
Acceptability (TAM)	Mean ≥ 3.5	Mean 3.0–3.49	Mean < 3.0
Usability (SUS)	Score ≥ 68	Score 60–67	Score < 60
Dropouts	≤20% dropout rate	21–29% dropout rate	≥30% dropout rate

Note. GO = criteria met for progression to definitive trial; AMEND = criteria met with modifications; STOP = criteria not met. Predefined success thresholds were based on widely used benchmarks in feasibility research, such as ≥80% session completion [69], SUS ≥ 68 [55], and TAM mean ≥ 3.5 [70].

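### Section 2.1 puts registration after the feasibility results are analysed, so progression rules that the article leaves unresolved could be settled with the data in view

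*Protocol article*

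**What the plan says.** Section 2.1 (Design) calls the study a feasibility trial and states that "a full protocol registration will be completed after analyzing feasibility outcomes and incorporating any necessary adaptations". It adds: "The trial registry identifier will be provided once the definitive protocol is submitted". No other section of the text shown gives a registry number or mentions an earlier or partial registration.

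The outcomes that precede registration are the study's main ones. Section 2.9.2 says "The primary aim of this study is to assess feasibility across multiple domains" and that "Progression criteria for feasibility outcomes are summarized in Table 3 and Figure 2". Table 3 gives GO, AMEND and STOP bands for eight domains, and its note says that "Predefined success thresholds were based on widely used benchmarks in feasibility research".

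Recruitment is described as still to come: the abstract says the study "will recruit 30 participants aged 9 to 17 years with ADHD". Section 2.12 reports prior ethical review: "The protocol has been approved by the Local Biomedical Research Ethics Committee".

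**The concern.** The sequence is stated, so this is not a detail that a condensed article has left to a fuller document. As written, feasibility results are analysed, the protocol is adapted to them, and only then is something registered. A registry entry made at that point cannot show which rules were fixed before the data were seen.

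The study applies formal progression criteria to a group of minors, and the result informs whether a randomised trial goes ahead. Where a rule is incomplete or has two versions, the team could choose the version once it knows which side of the line the study fell on, and the later entry would record that choice as the rule. At stake is how far the progression verdict can be trusted on those particular points.

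**Working it through.** No formula in the plan bears on this, and the plan gives no figure to reproduce. The check sets sections side by side, with short arithmetic on Table 3.

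**Step 1. Two readings of the Section 2.1 sentence.**
- It means the present study: registration follows analysis and records an adapted protocol.
- It means the later randomised trial: the order is then sensible for that trial, but nothing says that the present study is registered.

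On either reading, the document states no registry entry for this study before its data are analysed.

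**Step 2. What the article already fixes in public.** It names the feasibility domains, the T0/T1/T2 schedule (Table 2), and numerical cut-offs for eight domains (Table 3). A results paper can be checked against these.

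**Step 3. What it leaves unresolved.**

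*Recruitment gap.* Table 3 has GO at 70% or more, AMEND at 50–59% and STOP below 50%, so 60–69% has no verdict. In the other seven rows AMEND runs up to the GO boundary, so this looks like a slip. To show its size, assume that 30 consent and let n be the number of eligible families approached. The rate is 30/n.

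| n | 30/n | Table 3 verdict |
|---|---|---|
| 42 | 71.4% | GO |
| 43 | 69.8% | none |
| 50 | 60.0% | none |
| 51 | 58.8% | AMEND |
| 60 | 50.0% | AMEND |
| 61 | 49.2% | STOP |

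Every n from 43 to 50 has no verdict.

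*Recruitment denominator.* Section 2.9.2 divides by eligible participants; Table 3 divides by eligible people who were approached. As a hypothetical case, take 50 eligible, 42 approached and 30 consenting. The Table 3 definition gives 30/42 = 71.4%, which is GO. The Section 2.9.2 definition gives 30/50 = 60.0%, which has no verdict.

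*Retention.* Section 2.9.2 names completion of all assessments at T1 and T2; Table 3 joins the two time points with a slash. Neither says whether one joint percentage or two separate ones are judged. As a hypothetical case, 25 of 30 at T1 is 83.3% (GO) and 23 of 30 at T2 is 76.7% (AMEND).

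*TAM and SUS respondents.* Table 2 gives both instruments to four groups: children and adolescents, parents, teachers and occupational therapists. Table 3 gives one threshold per instrument and does not say whose mean is compared with it. Section 2.9.2 speaks of participant feedback, but Table 2 also gives the participant satisfaction questionnaire to all four groups, so the word does not settle it.

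**Step 4. Is there still time?** The abstract puts recruitment in the future, and the participant flow diagram (Figure 3) is to be filled in after data collection. On the text shown, registration before the data are analysed still appears possible.

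**The case against.** The strongest reply is that publication does much of what a registry would. The article sets out domains, instruments, time points and cut-offs while describing recruitment as still to come, and ethics approval is in place. A dropped domain or a moved cut-off would be visible. This stands. A reader might infer from Section 2.1 that nothing is prespecified, or that threshold drift in general cannot be excluded. The document does not support either inference.

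Second, the sentence may concern only the later trial. Section 2.1 ties the identifier to a definitive protocol, and the Table 3 note uses the same adjective for the trial that a GO leads to. Retrospective registration of this study is therefore one reading and not an established fact. Silence about this study's own registration remains.

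Third, the recruitment gap and the unnamed respondents are defects of Table 3, and registration alone would not cure them. Registering Table 3 unchanged would lock the gap in. This also stands, and the fix has to complete the table. Figure 2, to which Section 2.9.2 also refers for the progression criteria, is not shown and may resolve some of these points.

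Finally, a reader might infer that the progression decision is all the study produces. It is not: Sections 2.9.2 and 2.9.3 and the Discussion also plan qualitative findings for refining the interface, estimates of variability, and improvements to evaluation procedures.

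**Conclusion.** The point holds in limited form. On either reading of Section 2.1, no registry entry for this feasibility study is stated to exist before its outcomes are analysed. The practical exposure is confined to what the article leaves open: recruitment of 60–69% (43 to 50 eligible families approached, if 30 consent), two recruitment denominators, the combination of T1 and T2 retention, and the deciding respondents for TAM and SUS.

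Severity is modest. This is a single-arm study of 30 that disclaims efficacy, and no estimate, sample size or analysis changes. The change is still worth making because it is cheap and protects the progression decision.

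The conclusion assumes that no registration exists that the article fails to mention, which fits its statement that the identifier is still to come. It also assumes that Figure 2 does not settle the open points. It does not depend on what the cited reporting guidelines require.

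**What to change.** 1. Register this feasibility study before the first enrolment. If enrolment has begun, register now and before any outcome is analysed, stating the registration date and the recruitment status on that date.
2. Complete the Table 3 criteria in the article and carry them into the entry. Assign recruitment of 60–69% to a category (extending AMEND to 50–69% would match the other rows), choose one recruitment denominator, say whether retention is judged jointly or at T1 and T2 separately, and name whose TAM and SUS means decide. Include the T0/T1/T2 schedule.
3. Register the later randomised trial separately, with the adapted protocol.
4. Reword the Section 2.1 sentence to say that the feasibility study is registered in its own right, with its identifier, and that the definitive trial will be registered separately after adaptation.

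The cost is a few hours of registry work, one revised sentence and small edits to Table 3 and Section 2.9.2. No participants, visits or procedures are added.

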### 2.2. Study Setting

The study will be conducted by the local university, in collaboration with local hospitals, health centers, the child and adolescent mental health unit, and the educational guidance team specializing in severe behavioral disorders. The intervention sessions will be conducted entirely online through the DiverAcción website, accessible via computer or tablet, and supervised by therapists from the research team.

### 2.3. Participants and Recruitment

Purposive sampling will be used to ensure the representativeness of different profiles of children and adolescents with ADHD. Participants and their primary caregivers will be recruited through the local Specialized Educational Guidance Team for Severe Behavioral Disorders, which will distribute invitations through school guidance counselors. Additionally, neuropediatricians from local hospitals and health centers will collaborate.

Potential candidates who meet the criteria and express interest in participating will be informed. A researcher from the team will contact eligible participants by telephone to confirm their inclusion and explain the objectives and characteristics of the study.

#### 2.3.1. Inclusion Criteria

Age between 9 and 17 years.Functional proficiency in Spanish (oral and written).Primary educational or clinical diagnosis of ADHD.Intelligence quotient (IQ > 69). Intellectual functioning will be assessed using the Wechsler Abbreviated Scale of Intelligence—Second Edition (WASI-II) [31]. The WASI-II is a standardized abbreviated intelligence test designed for individuals aged 6 to 90 years. It provides an estimate of Full-Scale IQ (FSIQ) based on two subtests (Vocabulary and Block Design) or four subtests (Vocabulary, Similarities, Block Design, and Matrix Reasoning). The WASI-II demonstrates high reliability (α ≈ 0.90–0.95) and strong validity, with correlations exceeding r = 0.90 with the full WAIS-IV and WISC-V scales, making it suitable for research purposes where a brief yet accurate measure of intellectual functioning is required [32].T-score ≥ 65 on the BRIEF-2 Cognitive Regulation and Behavioral Regulation indices, reported by parents or teachers.Informed consent from the legal guardian and written assent from the minor.

